**Methods:**

This is a pilot, randomized, double-blinded study where sixty participants with PD will be randomized into one of two, cueing interventions: 1) personalized, step-synchronized tactile cueing and 2) tactile cueing at fixed intervals. Both cueing interventions use vibrotactile stimulation of wrist bands. During a laboratory study visit, we will measure cortical activity with a wireless, portable functional near-infrared spectroscopy system (fNIRS) during walking tasks. Gait will be assessed using inertial sensors placed on the limbs and trunk. In addition, in daily life, participants will use the same cueing mode at home. The primary outcomes include prefrontal & primary sensory cortex activity. Secondary outcomes are gait stride time, gait local dynamic stability, turn duration and trunk jerk during turning as metrics of gait automaticity in the laboratory. Daily life gait and turning are exploratory measures.

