### 3.4. Assessment procedures

#### 3.4.1. General procedures.

Fig 2 below illustrates the flow of study activities. After screening and randomization, the immediate effect of the cueing interventions will be assessed during a study visit to the laboratory (Visit 1) through measures of cortical activity and functional mobility. Additionally, clinical and cognitive scales will also be conducted during this visit.

The main outcomes will be measured in the ON-medication state (after approximately 1-hour from last intake) before and while using their assigned tactile cueing mode (personalized or fixed). During the assessment, participants will complete the following mobility tasks, first without cueing and then with cueing activated: 1) 2-minute walking, 2) 2-minute walking with a concurrent cognitive dual-task, 3) 1-minute 360 degrees turning in place, and 4) 1-minute 360 degrees turning in place with a concurrent cognitive dual-task.

The gait task consists of two minutes of walking back and forth along a 9-meter hallway at comfortable speed. The turning task involves alternating 360° turns (right and left) in place for one minute. The secondary cognitive task used in both dual-task conditions is a modified version of the Continuous Performance Test–AX (AX-CPT), which assesses attention and vigilance.

Throughout the mobility protocol, participants will wear a portable fNIRS system (Brite and OctaMon, Artinis) and three wireless inertial sensors (APDM Precision Motion, Clario) positioned on the posterior trunk and both feet to objectively measure cortical activity while performing gait and turning tasks.

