### 3.5. Statistical methods

#### 3.5.1. Power analysis.

We computed power to detect differences in a larger reduction of PFC activity during personalized, compared to fixed, tactile cueing. Furthermore, we predict that personalized cueing will show less activation of PFC versus fixed cueing (i.e., more automatic). We conservatively assume 54 subjects, 27 for each group (personalized and fixed training), will be included in this analysis, based on recruitment of 60, and allowing for modest dropout (> 10%). We computed power for a repeated-measures ANOVA model with 1 between and 1 within subject effect based on the Geisser-Greenhouse F-test (equivalent to a mixed model). Using patterns of HbO2 levels comparable to previously published results(ref Stuart and Mancini JNPT), assuming between-subject variance of 0.08, modest intra-subject correlation of 0.2, and level of significance at 0.05, we find that power is 82% for the test of between-subject effects (cueing group comparison), and 94% for the test of interaction (differential impact of dual-task versus single-task walking between the personalized- and fixed-cueing groups).

We also computed sample sizes required to achieve at least 80% power for detecting group differences of at least 0.50 SD for measures of walking and turning in daily life with ANCOVA models, conservatively assuming covariate R2 equal to 20%. We set level of significance to 0.02, which is the average alpha level when employing the Holm correction method over 6 outcomes (see below). Under these assumptions, 36 patients (18 per arm) are required to achieve 81.2% power. Thus, our plan to recruit 30 per arm will result in adequately-powered tests while allowing for missing/insufficient data or patient dropout. One of the goals of this trial is to generate preliminary estimates of sensitivity of daily life gait and turning quality due to a cueing intervention. These estimates ultimately will be used to inform power and sample size computations for a larger clinical trial. The small intervention proposed here (30 per group) is not designed to be a highly powered trial itself, but will make use of a randomized, two-group intervention design. All computations were conducted using PASS v15 (PASS 15 Power Analysis and Sample Size Software (2017), NCSS, LLC).

We are not planning interim analysis, and we are not expecting to stop the recruitment early.

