#### 3.5.2. Statistical analysis.

The primary outcome will compare PFC and sensory cortex HbO2 while walking and turning between personalized tactile cueing and fixed tactile cueing groups measured during Laboratory Visit 1, without and with cueing. We will average the HbO2 concentrations over 2-minutes of walking (and over 1-minute of 360-degree clockwise and counterclockwise turning), then compare within-subject effects (baseline versus cueing) and between-subject effects (personalized versus fixed cueing) in a repeated measures analysis. Specifically, we will apply mixed-effects models with HbO2 levels (averaged over walking bout) for each person at each assessment time point as the dependent variable. We will include as independent variables: (i) indicator variable for group assignment (personalized or fixed cueing), (ii) indicators for time points (baseline, cueing), and (iii) group by assessment interaction terms. Randomization stratification variables, Hoehn and Yahr, FOG and cognitive status, will be entered into the model as covariates. A random subject intercept will account for correlation between the two repeated measurements within each subject.

Similar linear mixed effects models will be used to demonstrate improvement in walking and turning metrics in the laboratory (carried out with the fNIRS measurements), secondary outcomes. Significance level will be set at 0.05 for testing whether coefficients are different from 0 for primary and secondary outcomes.

We will employ similar linear mixed effects models to investigate whether the two cueing modalities will result in different improvements of walking and turning during daily life. This is an exploratory analysis. For the week of daily mobility without and with cueing, we will summarize walking and turning measures at home (outlined on Table 1) by computing the average over 7 days of daily activity, considering only the recordings with more than 7 hours per day and at least 5 days (Table 1). Randomization stratification variables, Hoehn and Yahr, freezing of gait and cognitive status, will be entered into the model as covariates. Additional covariates would be the life space assessment and activity levels. The effect sizes from models fit for this pilot study will be used to determine the number of subjects required for a future clinical trial.

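### Prefrontal and sensory cortex activity are both primary, in walking and turning, and unspecified coefficients are tested at an unadjusted 0.05 with no rule for combining the results

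*Protocol article*

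**What the plan says.** - **Primary outcomes.** The abstract says "The primary outcomes include prefrontal & primary sensory cortex activity". Table 1 marks the same two regions in bold as primary. Neither ranks them.
- **Conditions.** Under Statistical analysis: "The primary outcome will compare PFC and sensory cortex HbO2 while walking and turning between personalized tactile cueing and fixed tactile cueing groups". General procedures (3.4.1) lists the tasks: "1) 2-minute walking, 2) 2-minute walking with a concurrent cognitive dual-task, 3) 1-minute 360 degrees turning in place", and then "4) 1-minute 360 degrees turning in place with a concurrent cognitive dual-task". Each is done first without and then with cueing.
- **Model.** The plan is to "compare within-subject effects (baseline versus cueing) and between-subject effects (personalized versus fixed cueing) in a repeated measures analysis". The mixed model has indicators for group and for time point, their interaction, covariates and a random subject intercept. It has no term for single versus dual task.
- **Test rule.** "Significance level will be set at 0.05 for testing whether coefficients are different from 0 for primary and secondary outcomes".
- **Planning of the primary.** Power analysis plans PFC at 0.05 with 27 per arm. It states 82% power for the between-group effect and 94% for a group by single/dual-task interaction in walking.
- **Planning of daily life.** For home gait and turning measures, the same section says: "We set level of significance to 0.02, which is the average alpha level when employing the Holm correction method over 6 outcomes (see below").

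**The concern.** Two regions in at least two activities are primary, and each gets its own test at 0.05. Nothing says whether one success is enough, whether all are needed, or which is tested first. As written, the rule does not hold the overall error of the primary family at 5%.

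The word coefficients adds a second ambiguity. The model yields a group, a time and an interaction coefficient, and they answer different questions. If the choice is left open, a result that does not compare the two cueing modes as randomised could be read as the primary finding. At stake is whether the trial can support its stated hypothesis about automaticity, and how far its effect sizes should be trusted when the next trial is planned.

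**Working it through.** **1. Number of primary comparisons**

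- As the Statistical analysis section words it: 2 regions × 2 activities = 4.
- If each of the four tasks in section 3.4.1 is analysed separately: 2 × 4 = 8.
- Smallest reading, one test per region: 2.

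These counts take one coefficient per model.

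**2. Chance of at least one false positive, each test at 0.05**

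For m independent tests this is 1 − 0.95^m:

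- m = 2: 1 − 0.9025 = 9.8%
- m = 4: 1 − 0.8145 = 18.5%
- m = 8: 1 − 0.6634 = 33.7%

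The tests share subjects, so they will be correlated. The article gives no correlation between regions or tasks, so the values below are assumptions. They come from simulating equally correlated normal test statistics (400,000 draws, two-sided limit 1.96).

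| Tests | r = 0 | r = 0.2 | r = 0.5 | r = 0.8 |
|---|---|---|---|---|
| 2 | 9.8% | 9.5% | 9.1% | 7.9% |
| 4 | 18.5% | 17.9% | 15.6% | 11.4% |
| 8 | 33.7% | 31.8% | 25.0% | 15.8% |

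**3. What each coefficient estimates**

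Write the mean as b0 + b1·G + b2·T + b3·G·T. Take G = 1 for personalized cueing and T = 1 for the cued assessment, coded 0/1 with baseline as reference.

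- b1 is the group difference before cueing. Randomisation makes it zero in expectation, so it carries no treatment effect.
- b2 is the change in the fixed-cueing arm. Cued trials always follow uncued ones, so cueing is confounded with order (practice, fatigue, signal drift).
- b3 is the difference between arms in that change. The order is the same in both arms, so b3 is the randomised effect.

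Under a coding centred at zero, the group coefficient becomes b1 + b3/2. This mixes the baseline difference with half the effect, so the meaning of a group test depends on a coding choice as well.

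**4. Whether the power section settles the choice**

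Its opening aim, a larger PFC reduction with personalized cueing, corresponds to b3. The 82% is for a between-group effect. The 94% is for group by single/dual task, a term the analysis model does not contain. The 82% and 94% cannot be reproduced, because the assumed HbO2 means are not given.

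**5. Cost of adjusting instead of ordering**

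With 27 per arm, 82% power at 0.05 in a two-group comparison corresponds to about 0.80 SD of the tested contrast. At the same effect, Bonferroni (the first Holm step) gives:

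- 0.05/2 = 0.025: 73%
- 0.05/4 = 0.0125: 64%
- 0.05/8 = 0.00625: 54%

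A first test in a fixed sequence keeps 0.05. It keeps the 82% only if it is the test that was powered.

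**6. The Holm figure**

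Average alpha over six steps = (0.05/6) × (1 + 1/2 + 1/3 + 1/4 + 1/5 + 1/6) = (0.05/6) × 2.45 = 0.0204, which reproduces the stated 0.02. The text that follows describes no Holm procedure and lists no six outcomes. Table 1, which the daily-life analysis uses, holds 3 means + 3 CoVs + LDS = 7 gait metrics and 4 turning metrics, 11 in all.

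**The case against.** **Intent is visible.** The power section aims at a larger PFC reduction with personalized cueing. The Discussion says that the hypothesis is supported if PFC falls and sensory activity rises only with personalized cueing. This weakens any claim that one hit anywhere would be reported as success. It stands as evidence of intent, but neither statement is a testing rule. The Discussion also frames its condition as change from baseline within each arm, not as the between-arm interaction. Even as a formal conjunction it would leave the task open: if one region truly responds, a free choice among 2 to 4 tasks allows 9.8% to 18.5% (independent tests) for the other.

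**The count of eight is an inference.** This stands. The analysis section says walking and turning and does not say how the dual-task versions enter. Four is the plain reading and eight the upper one.

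**Holm was never meant for the cortical outcomes.** This also stands. A reader might infer that the missing Holm step causes the primary inflation, or that the trial plans at 0.02 but tests at 0.05. The document supports neither. PFC is planned and tested at 0.05. The 0.02 belongs to the daily-life measures, which are labelled exploratory and to which the 0.05 sentence does not refer.

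**It is a pilot.** This lowers the severity, and unadjusted secondary outcomes are not pressed here. It does not remove the point, because the article states a significance level, 82% and 94% power, and a finding that would support the hypothesis.

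**A separate analysis plan may settle it.** Such a plan could add detail, but the article itself fixes 0.05 for these coefficients and points to a correction that does not follow.

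**Conclusion.** The point holds in this form. The primary family has 4 comparisons, up to 8, each at 0.05 without ordering, conjunction or adjustment. The chance of at least one false-positive primary result is about 18.5% for 4 independent tests (about 16% at correlation 0.5) and about 34% for 8 (about 25% at 0.5). These figures assume that no effect is real, that there is one coefficient per model and that any single success counts. The correlations are assumed, and every value in the range examined exceeds 5%. The group-by-time interaction is the only coefficient that estimates the randomised effect, and the plan does not name it. The reading of the group coefficient as a baseline difference assumes 0/1 coding.

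The Holm reference is a separate internal inconsistency about exploratory outcomes. Severity: should be fixed, given the pilot status.

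**What to change.** **In Statistical analysis, for the primaries**

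1. State that the primary test is the group-by-time interaction, two-sided.
2. Fix one rule across the primaries. One option is PFC during walking first at 0.05, since that is the outcome the power section addresses. Sensory cortex is then tested only if PFC succeeds, and turning comes later in the sequence or becomes secondary. Holm across the primaries would also do, as would a formal PFC-and-sensory conjunction following the Discussion, with the task fixed. Which of these to use is the sponsor's choice.
3. State how single- and dual-task data enter. Averaging them gives one test per region and activity, but drops from the primary test the single/dual differential that was powered at 94%. If that differential matters, add a task term and give it a place in the rule.

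**For daily life**

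List the six outcomes and describe Holm in the analysis section. Otherwise remove the reference and restate the alpha on which that power calculation rests.

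**Cost**

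This is wording only, with no new data or visits, and should be done before any unblinded analysis. Fewer results can be called significant. In a sequence, sensory cortex and turning depend on PFC succeeding; under Holm, the power of each test falls as shown in the working.

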## 4. Discussion

This project aims to characterize the cortical correlates of gait automaticity in PD, evaluate the effects of personalized, versus fixed, tactile cueing on automaticity and explore the feasibility and efficacy of using tactile cueing to improve gait and turning in daily life. The technologies used pose minimal risk and findings could inform more effective, individualized rehabilitation strategies to reduce falls and enhance mobility.

If we find a decrease in PFC activity and an increase in sensory activity only with personalized, closed-loop cueing, and not fixed, open-loop cueing, compared to baseline, this will support our hypothesis that personalized, closed-loop feedback improves gait automaticity. However, we expect to find improvements in walking and turning, measured in the laboratory (reduced stride-time variability, increased gait speed, reduced turning duration and turning jerkiness) with both cueing interventions. We will investigate which cueing modality is superior in improving gait and turning during daily life, when less attention is on gait [75]. If we find a a small effect size, then a greater sample size will be needed for a future, randomized, placebo-controlled clinical trial to improve daily mobility in people with PD.

This trial incorporates several innovative elements. It is among the first to combine portable fNIRS with wearable inertial sensors to assess both cortical activity and gait and turning measures in the laboratory, as well as investigating feasibility of using cueing and measuring effects on gait and turning in the real-world. The use of personalized, closed-loop tactile cueing, which delivers stimulation in real time based on the individual’s gait cycle, represents a major advancement over conventional fixed (open-loop) cueing systems. Unlike auditory or visual cues, the tactile modality targets proprioceptive pathways and may better engage subcortical circuits involved in gait automaticity [38,40].

Another aspect of innovation is the fact that our cueing system is standalone, app-free design, allowing users to benefit from tactile cueing without relying on smartphones or external devices. The tactile stimulus occurs on simple bracelets on the wrists, which are easy to don and provides perceptible vibration to people with PD, who usually cannot detect vibration on the feet [76]. The cueing system has a simple switch to turn the stimulation on or off. This simplicity is especially important for people with Parkinson’s disease, who may experience cognitive or motor challenges that make app navigation difficult. By eliminating the need for digital interfaces, the system may enhance usability, accessibility, and real-world adherence, making it a practical solution for unsupervised use in daily life. The device’s personalized, closed-loop algorithm still operates in real time based on the user’s gait, delivering tailored cues, while maintaining a user-friendly, low-tech interface, which is a novel feature in the field of gait rehabilitation.

Furthermore, using instrumented socks allows for unobtrusive and continuous monitoring of gait in daily life, providing a rich dataset to evaluate how cueing affects mobility outside the laboratory. Likewise, the sensor on the elastic belt around the waist provides accurate measures of turning quality in daily life. By bridging neural, behavioral, and ecological data, this study can help next-generation, personalized rehabilitation strategies in PD and as well as other groups with gait impairments. Gait automaticity, or the ability to multitask while walking, is a critical, functional skill that may be improved with the addition of appropriate rehabilitation, such as cueing.

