## 2. Objectives

The primary objective of this trial is to assess immediate changes in cortical activity during walking with two types of tactile cueing in people with PD, and whether these changes are accompanied by improvement in gait and turning (laboratory testing). We hypothesize that personalized tactile cueing will reduce PFC activity (improve automaticity) and reduce gait variability (as well as improve gait and turning speed). We also expect to observe increased activity in the primary sensory cortex with this type of personalized cueing that may require sensorimotor planning. In contrast, we predict that the fixed cueing will increase PFC activity and increase gait variability (need for more attention to the cues). An exploratory objective is to evaluate the feasibility and potential benefits of using tactile cueing during daily life.

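### The stated condition for supporting the primary hypothesis contrasts two changes from baseline, one per arm, and the group-by-assessment interaction already in the model is not made decisive

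*Protocol article*

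**What the plan says.** Four places in the protocol article bear on this.

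- **Discussion (section 4).** Support for the hypothesis is tied to a PFC decrease and "an increase in sensory activity only with personalized, closed-loop cueing, and not fixed, open-loop cueing, compared to baseline, this will support our hypothesis". The reference for each arm is its own uncued baseline. No other sentence in the article says which result would count as support for the primary hypothesis.
- **Statistical analysis (3.5.2).** The mixed model has group, time point and "iii) group by assessment interaction terms". The section announces that it will "compare within-subject effects (baseline versus cueing) and between-subject effects (personalized versus fixed cueing) in a repeated measures analysis", without ranking these effects. It adds: "Significance level will be set at 0.05 for testing whether coefficients are different from 0 for primary and secondary outcomes". No single coefficient is named as the test of the hypothesis.
- **General procedures (3.4.1).** Every participant does the tasks "first without cueing and then with cueing activated".
- **Gait variability.** In the Objectives (section 2), "we predict that the fixed cueing will increase PFC activity and increase gait variability". In the Discussion, the expected laboratory improvements are "reduced stride-time variability, increased gait speed, reduced turning duration and turning jerkiness) with both cueing interventions".

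**The concern.** A change found in one arm and not found in the other does not show that the arms differ. If both arms shift by the same true amount, chance alone can put one over the 0.05 line and leave the other short of it. Anyone applying the Discussion sentence literally could then report that personalized cueing improves automaticity when the modes do not differ.

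The testing order adds to this. Because the uncued tasks always come first, practice, fatigue or time since the last dose can contribute to a shared change in both arms. The randomized contrast cancels such a shift; two separate changes from baseline do not.

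The conflict over gait variability is a smaller, related matter. With opposite predictions in print for the fixed arm, a change in either direction there can be described as expected.

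**Working it through.** **The plan's own figures.** The Power analysis section gives 82% for the between-group effect and 94% for an interaction, with 27 per arm. The assumed HbO2 means are not printed, so neither figure can be recomputed. Solving backwards with a noncentral F test (1 and 52 df, two-sided 0.05):

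- 0.08 read as total variance, correlation 0.2: 82% needs a group difference of 0.175, and 94% needs an interaction contrast of 0.349.
- 0.08 read as the subject component (total 0.08/0.2 = 0.40): 0.391 and 0.780.

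The interaction powered there is group by task (dual versus single), not group by assessment (baseline versus cueing).

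**Inputs for the check.** 27 per arm, variance 0.08 and correlation 0.2 come from the Power analysis section. The 0.05 level comes from the Statistical analysis section; two-sided is assumed. The size of a change shared by both arms is not in the document, so a range is shown.

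**One region.** SD of change = √(2 × variance × (1 − 0.2)).

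- Total variance 0.08: √(2 × 0.08 × 0.8) = 0.358; standard error within an arm 0.358/√27 = 0.069.
- Total variance 0.40: √(2 × 0.40 × 0.8) = 0.80; standard error 0.80/√27 = 0.154.

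Let p be the power of the paired t-test within one arm, in the hypothesised direction. With equal true change in both independent arms, the chance that only the personalized arm is significant is p(1 − p).

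| Reading of 0.08 | Shared change | p | p(1 − p) |
|---|---|---|---|
| Total variance | 0.10 | 0.287 | 20.5% |
| Total variance | 0.14 | 0.499 | 25.0% |
| Total variance | 0.20 | 0.798 | 16.1% |
| Subject component | 0.14 | 0.139 | 12.0% |

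The maximum of p(1 − p) is 0.25, at p = 0.5. It falls to about 6% when p is 94%. Simulation (40,000 trials per setting) agrees. In the same simulated trials, the between-arm test of change wrongly favours personalized cueing in about 2.5%, whatever the shared change.

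**Two regions.** The sentence needs PFC to fall and sensory activity to rise. Take the strict reading: both significant in personalized, neither in fixed. Let r be the correlation between the two changes, each signed in its hypothesised direction. Because the directions are opposite, a positive correlation of raw HbO2 changes makes r negative. At p = 0.5 the chance that both are significant in an arm is q = 1/4 + arcsin(r)/(2π). The chance that neither is significant is also q, so the rate is q².

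| Raw HbO2 correlation | r | q | q² |
|---|---|---|---|
| +0.9 | −0.9 | 0.072 | 0.5% |
| +0.5 | −0.5 | 0.167 | 2.8% |
| 0 | 0 | 0.250 | 6.3% |
| −0.5 | 0.5 | 0.333 | 11.1% |
| −0.9 | 0.9 | 0.428 | 18.3% |
| −1 | 1 | 0.500 | 25.0% |

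On a looser reading (both in personalized, not both in fixed), the rate is q(1 − q), which also cannot exceed 25%.

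**The case against.** The best defence is that the Discussion sentence is interpretive prose. It does not mention significance, p-values or separate tests. Read plainly, a pattern seen in one arm and not the other describes an interaction, and that fits the Objectives, where PFC is predicted to move in opposite directions. The Statistical analysis section compares the groups without and with cueing and fits the interaction. All of this stands. It limits the point to the stated criterion, but does not remove it: no passage makes the interaction decisive, and within- and between-subject effects are listed as equals.

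A reader might infer more, and the document does not support it:

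- *That the between-arm analysis is missing.* The term is in the model.
- *That the fixed order biases the trial.* Both arms share it, so it affects within-arm changes and not the randomized contrast.
- *That a true difference would be missed because both arms changed.* The sentence gives a sufficient condition. It does not say that other results fail to support the hypothesis, and the interaction remains available.
- *That 25% is the false-support rate.* It is the one-region maximum, at a change chosen to give 50% within-arm power. The sentence requires two regions, and if raw HbO2 changes correlate positively the strict rate is close to zero.
- *That the behavioural hypothesis cannot be refuted.* Both sections predict lower variability with personalized cueing, which can fail. Only the fixed-arm direction is contradictory.

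**Conclusion.** The point holds as a defect in the stated criterion for support. Taken with the 0.05 coefficient tests, the Discussion sentence can be satisfied when both arms change equally: up to 25% of trials for one region, against about 2.5% for the interaction. For the strict two-region reading the range is near 0 to at most 25%.

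These figures rest on four assumptions: that finding a change means two-sided significance at 0.05 within an arm, the size of the shared change, the reading of the variance 0.08, and the between-region correlation. The last is absent from the document, so no single two-region rate should be quoted.

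The contradiction over gait variability under fixed cueing needs no assumption; it is visible on the page.

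**What to change.** 1. In the Statistical analysis section and the Discussion, state that support for the hypothesis rests on the group-by-assessment (baseline versus cueing) contrast, reported with its estimate and 95% CI, for PFC and for sensory cortex.
2. Describe within-arm changes from baseline as descriptive.
3. If the two regions are to be tested in sequence, declare the order; the document currently gives none.
4. Note in the Power analysis section that the 94% refers to the group-by-task interaction, and that power for the contrast in item 1 is not stated.
5. Before unblinding, settle one directional prediction for gait variability under fixed cueing and use it in both the Objectives and the Discussion.

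The cost is a few sentences. The model and the data collection stay as they are. Nothing here calls for a different sample size, but the power of the deciding contrast would need to be worked out and reported.

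### The stated condition for support sets two within-arm changes side by side and does not use the randomised contrast that the model already contains

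*Protocol article*

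**What the plan says.** The condition for support is in section 4, Discussion: a fall in PFC activity and a rise in sensory activity "only with personalized, closed-loop cueing, and not fixed, open-loop cueing, compared to baseline, this will support our hypothesis". The hypothesis in question is that personalized feedback improves automaticity. Each arm is judged against its own baseline. The difference between the arms in their change is not mentioned.

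The Statistical analysis section plans to "compare within-subject effects (baseline versus cueing) and between-subject effects (personalized versus fixed cueing) in a repeated measures analysis". The mixed model has a group indicator, time indicators and "group by assessment interaction terms". The threshold is given once: "Significance level will be set at 0.05 for testing whether coefficients are different from 0 for primary and secondary outcomes". No coefficient is named as the one that decides the primary question.

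The Power analysis section has a between-arm target: "We computed power to detect differences in a larger reduction of PFC activity during personalized, compared to fixed, tactile cueing".

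The General procedures section fixes the order at Laboratory Visit 1. Every participant does all mobility tasks without cueing first and then repeats them with cueing. The Intervention section adds a 15-minute acclimatization before the cued assessment.

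**The concern.** A significant change in one arm and a non-significant change in the other is not evidence that the arms differ. Two arms with the same true change will often give different verdicts by chance, most often when within-arm power is near one half.

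The fixed order makes this a practical matter here. Practice, fatigue and settling in are part of each arm's change from baseline, whichever cueing mode was assigned. The randomised comparison removes what is common to both arms; a within-arm comparison does not. If the Discussion sentence is used as written, a shared change could be reported as an effect specific to personalized cueing. The primary conclusion would then not rest on randomisation, although the planned model supplies the contrast that would put it there.

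**Working it through.** **The plan's own figures.** The Power analysis section states 82% power for the group comparison and 94% for an interaction. The HbO2 means behind them are not given, so they cannot be recomputed forward. Solved backwards (27 per arm, variance 0.08, correlation 0.2, two-sided 0.05), they imply a group difference of about 0.175 and a difference of changes of about 0.349. The 94% refers to dual-task versus single-task by group, so it does not describe the group-by-assessment term. No error rate is stated for the Discussion's condition.

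**Inputs.** From the Power analysis section: 27 per arm, variance 0.08, intra-subject correlation 0.2. From the Statistical analysis section: level 0.05, read as two-sided. Assumptions: 0.08 is the total variance of one measurement; the two arms have the same true change; finding a change means significance in the predicted direction.

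**Step 1: standard errors.** SD of the within-person change = √(2 × 0.08 × (1 − 0.2)) = 0.358. Standard error of one arm's mean change = 0.358/√27 = 0.069. Standard error of the difference between arms = 0.358 × √(2/27) = 0.097.

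**Step 2: PFC alone.** Within-arm power p comes from the noncentral t distribution with 26 df and noncentrality change/0.069. The arms are independent, so P(personalized significant, fixed not) = p(1 − p).

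| Common true change | p | p(1 − p) |
|---|---|---|
| 0 | 2.5% | 2.4% |
| 0.05 | 10.4% | 9.3% |
| 0.10 | 28.7% | 20.5% |
| 0.14 | 49.9% | 25.0% |
| 0.20 | 79.8% | 16.1% |
| 0.25 | 93.8% | 5.9% |

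The maximum, 0.5 × 0.5 = 25%, falls at a change of 0.14. That is 0.14/√0.08 ≈ 0.5 SD, and smaller than the group difference of about 0.175 implied by the stated 82%. A different reading of the variance would move the change at which the peak occurs, but not its height. In simulation (40,000 trials) the rate at 0.14 was 24.6% to 24.8%.

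**Step 3: both outcomes required, as the Discussion says.** Take the same power p for each outcome, and the outcomes as independent.

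- If the fixed arm need only lack the full pattern: p²(1 − p²). At p = 0.5 this is 0.25 × 0.75 = 18.8%. At p = 0.8 it is 0.64 × 0.36 = 23.0%. Between them it peaks at 25% near p = 0.71.
- If the fixed arm must show neither change: p²(1 − p)². At p = 0.5 this is 0.25 × 0.25 = 6.3%. At p = 0.8 it is 0.64 × 0.04 = 2.6%. With correlated outcomes it rises: at a change of 0.14, simulation gave 11% at correlation 0.5 and 20% at 0.95.

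**Step 4: the interaction test on the same data.** Under equal changes it is significant in 5% of trials, 2.5% in favour of personalized cueing, whatever the size of the common change. Simulated: 4.8% to 5.2% two-sided, and 2.4% to 2.7% in favour of personalized cueing.

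**The case against.** The best defence is that the sentence is interpretive prose in a Discussion. It names no test and no threshold and does not ask for non-significance. The Statistical analysis section specifies a single mixed model with the interaction, not separate paired tests, and the Power analysis section shows between-arm intent. On that view the sentence merely describes a non-zero interaction with little change under fixed cueing. This stands in part: the right term is in the model, and the two-verdict reading borrows its threshold from another section. It does not settle the matter, because no coefficient is named as decisive and no other sentence says which result will count as support.

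It can also be said that the supported claim is that personalized feedback improves automaticity, not that it beats fixed cueing. If both modes truly lower PFC activity, that claim is true. This also stands in part. The pattern misleads when it is read as specific to personalized cueing, or when the shared fall comes from repeating the tasks.

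The common change is an assumption. The Objectives predict the opposite direction under fixed cueing, and with no common change the rate is only about 2.4%.

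A reader might infer that the plan would discard a real between-arm difference whenever the fixed arm also improves. The text does not support that. It says that support follows if the pattern is found; it does not say that other patterns give none.

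**Conclusion.** The point holds as a fault in the stated interpretation, not in the model. If the Discussion's condition is applied as significance verdicts at 0.05, it does not test whether the arms differ.

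Its size depends on three things that the documents leave open: the common change, the correlation between the two cortical outcomes, and what the fixed arm must fail to show. The 25% is a worst case and should not be quoted as the expected error rate. On the strictest two-outcome reading with independent outcomes, the rate is about 3% to 6% at p = 0.8 and 0.5.

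Severity is moderate. The trial is a pilot, the model needs no change, and an SAP that is not shown may name the decisive coefficient. It still concerns the primary objective, and the published wording invites the wrong comparison.

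**What to change.** Reword the Discussion sentence, and carry the same wording into the analysis plan:

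- Any claim for personalized over fixed cueing rests on the group-by-assessment term for PFC HbO2 in the predicted direction, and likewise for sensory cortex HbO2.
- Each arm's change from baseline is reported as a model estimate with its confidence interval. A non-significant change in the fixed arm is not a condition.

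This takes one or two sentences, with no new data and no change to the model. The cost is that some results with significance in one arm only will no longer count as support. The contrast is also less precise than a single arm's change: its standard error is √2 times as large (0.097 against 0.069 under the assumptions above).
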